# Article

Over that last decades, there has been a quest to find the missing heritability of obesity. Twin and adoptions studies indicate a strong genetic contribution at the individual level with heritability estimates for obesity between 40 and 60%. ^1, 2^ Although relying on family observations, this rough estimate encompasses both the additive effect of genes and multiplicative effects such as gene-environment interplay. ^3^ In contrast with these estimates, genome-wide association studies (GWAS) have identified genetic variants that explain a mere fraction of the additive effect of genes that accounts for 2-5% of variation in BMI.

Recently, a genome wide polygenic score (GPS) has been developed for BMI that combines ‘all available common variants into a single quantitative measure of inherited susceptibility’. ^4^ Unlike the genetic risk score (GRS) based on 97 genetic variants reaching genome-wide significance for BMI^5^, the GPS encompasses over two million genetic variants associated with BMI. By using most of the information in our genome, we can explain a larger variation of BMI in the population. This powerful new tool retrieves some of the missing heritability of obesity by increasing variance from 2-5% in GWAS to 9% in GPS. This translates to a 13-kg weight gradient in today’s middle-aged adults solely due to genetic differences.^4^ For the first time, any ‘reasonably sensitive observer’ can appreciate the genetic contribution to obesity.^6^

The GPS has room for refinement and accounts for only the additive effect of common gene variants. However, it can be used as a tool for exploring gene-environment interactions, ‘which are known to be important for genetic effects on’ obesity.^7^ Previous studies have suggested that genetic variants known to predict BMI had larger effects after the onset of the obesity epidemic than before, however, they are limited by self-reported BMI, short follow-up time, a selected older population ^8, 9^ and by weaker genetic instruments. (Ref .[name]/[name] in print BMJ)

Using a comprehensive dataset with the largest sample size and range of ages and years to date, we aim to study the absolute risk for obesity and heavier body weight for individuals in the top decile of the GPS score. We will investigate if recent secular trends affected this risk among the most genetically predisposed. We also aim to demonstrate the stability of the GPS in an external sample and before and after the obesity epidemic.

## Method:

*Study population*

The study is based on data from participants in the Nord-Trøndelag Health Study (HUNT, 1984-2008) linked to previous height and weight measurements for the same individuals in the Tuberculosis Screening Program (1963-75). We will include 118,959 HUNT participants aged 13-80 with valid height and weight measurements of whom 67,305 had genetic data available.

*Weight and Obesity*

The main outcomes will be weight and the prevalence of obesity. Body mass index (BMI) will be a secondary outcome with corresponding results shown in the supplementary materials. We chose to focus on weight in relation to men and women of average stature as this outcome is comprehendible for the general reader. Participants were measured wearing light clothes and without shoes. Weight was measured to the nearest half kilogram and height was measured to the nearest centimeter^10^. We will calculated BMI as weight in kilograms per meter squared*.* The World Health Organization defines overweight as BMI greater than or equal to 25 and obesity as BMI greater than or equal to 30 ^11^. We will calculate a BMI z-score for participants younger than 18 years of age as BMI strongly relates to longitudinal growth. Here we will use the International Obesity Task Force (IOTF) reference to adjust for age and gender^12^.

*Genotyping, derivation and validation of the Genome-Wide Polygenic Score*

For adult participants in HUNT2 and HUNT3, genotyping was performed with one of three different Illumina HumanCoreExome arrays (HumanCoreExome12v1.0, HumanCoreExome12 v1.1, and UM HUNT Biobank v1.0).^13^

We will use the genome-wide polygenic score (GPS) for BMI recently derived, validated and tested by Khera et al. This GPS provides a ‘single quantitative measure of inherited susceptibility’ by combining all available common variants (minor allele frequency >=1%) for BMI.^4^

The GPS was derived using a computational algorithm for 2.1 million genetic variants identified to be associated with BMI in over 300,000 individuals in the Giant Investigation of Anthropometric Traits consortium (GIANT)^4, 5^. Please see Khera et al. for more detail on derivation and validation of the GPS.^4^ We will use weights from Khera et al. that were estimated using the UK Biobank. We will divide the study population into ten equal sized groups.

*Statistical Analysis*

We will analyze longitudinal trajectories in obesity (BMI >30 kg/m^2^ as a dichotomous variable) using linear mixed models with observations clustered within individuals, and with a random slope for age. We will adjust for age using linear splines. The analyses will be performed separately for men and women. Based on this model, we will graph the estimated prevalence of obesity for the highest compared to lowest tenth of genetic susceptibility for chosen ages at each decade for men and women. Using a linear model on a dichotomous outcome gives us a linear probability model. The results will be easily interpretable, but we risk having confidence intervals including impossible values of probabilities below null. We will use a similar model to analyze longitudinal trajectories in weight (kg) in relation to men and women of average height.

We will perform several sensitivity analyses. First, we will analyze the associations between genetic risk, age and time using generalized estimation equation (GEE). This will allow us to use a logistic model. By use of postestimation commands (margins), we can predict the probability of obesity in the population for different groups. Second, we will assess the probability of having genetic data available (i.e. participating in HUNT2 or HUNT3) based on the obesity status of participants in TBC-screening. An association will indicate a possible selection bias, and will be handled by restricting the sample to younger cohorts. Third, we will assess the association between GPS and the natural logarithm of BMI. We will do this to approximate the relative difference in BMI rather than the absolute difference in BMI between the top and bottom tenth of genetic predisposition.

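### The stated models cluster only on the individual and name no term for relatedness, genotyping array or ancestry, so slope intervals are probably slightly too narrow and structure is left unchecked

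*Protocol*

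**What the plan says.** The Statistical Analysis part of the protocol's Method section sets the main model as "linear mixed models with observations clustered within individuals, and with a random slope for age". On covariates it says "We will adjust for age using linear splines", and on sex "The analyses will be performed separately for men and women". The weight model covers "longitudinal trajectories in weight (kg) in relation to men and women of average height". The obesity results are to be graphed for "the highest compared to lowest tenth of genetic susceptibility for chosen ages at each decade for men and women".

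Three sensitivity analyses follow: a logistic generalized estimating equation (GEE) model with genetic risk, age and time; a check on selection into genotyping; and a log-BMI analysis. None mentions relatives, array or ancestry, and the GEE analysis names no family cluster.

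The part of Method on genotyping states that for adults in HUNT2 and HUNT3 "genotyping was performed with one of three different Illumina HumanCoreExome arrays". Everyone is then placed in ten equal groups on a score whose weights come from an external sample. The study population is one regional health study, ages 13-80, "of whom 67,305 had genetic data available", with measurements reaching back to 1963-75.

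**The concern.** A regional study that spans these ages and decades will almost certainly contain parents, children and siblings, although the protocol gives no count. The exposure is inherited, so relatives resemble each other on the GPS. By the protocol's introduction, the score explains 9% of BMI variance against a heritability of obesity of 40-60%, so most inherited resemblance stays in the residual. When exposure and residual are both correlated within families, a model that treats different people as independent gives standard errors that are too small.

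Array and ancestry raise a separate question of bias. If the score sits higher on one array or in one ancestry subgroup, and that group also differs in BMI for other reasons, part of the difference is credited to the GPS. If the grouping also follows birth cohort, it could reach the study's central claim, that risk among the most predisposed changed over time.

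**Working it through.** The protocol states no power, sample-size or interval-width figure, so there is nothing to reproduce. The check sizes each consequence.

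**Inputs from the protocol:** heritability h² = 0.40 to 0.60; BMI variance explained by the GPS, R² = 0.09; 67,305 genotyped; separate models by sex.

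**Assumptions:** relatives are first-degree, with GPS correlation 0.5; they resemble each other only through additive genes; the obesity heritability is applied to BMI; m is the number of same-sex relatives per family in one model. The protocol gives no value for m.

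**1. Relatedness and the GPS slope**

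Residual correlation between relatives: ρ = (0.5·h² − 0.5·R²)/(1 − R²).
- h² = 0.40: (0.200 − 0.045)/0.91 = 0.170
- h² = 0.60: (0.300 − 0.045)/0.91 = 0.280

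Design effect: DE = 1 + (m − 1)·0.5·ρ. The standard error should be multiplied by √DE, and the true coverage of a nominal 95% interval is 2Φ(1.96/√DE) − 1.

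| m | DE | √DE | Coverage |
|---|---|---|---|
| 1.25 | 1.021-1.035 | 1.01-1.02 | 94.8-94.6% |
| 2 | 1.085-1.140 | 1.04-1.07 | 94.0-93.4% |
| 3 | 1.170-1.280 | 1.08-1.13 | 93.0-91.7% |
| 5 | 1.341-1.560 | 1.16-1.25 | 90.9-88.3% |

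At m = 2 the effective number is 67,305/DE, about 59,000 to 62,000.

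**2. Relatedness and the planned tenth-versus-tenth contrast**

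The formula above is for a slope, so the contrast was simulated: 6,000 people, 1,500 runs, sibling families of size m, one measurement each, obesity prevalence near 20%. Ratio of true to naive standard error:

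| m | Continuous outcome | Obesity (0/1) |
|---|---|---|
| 1 (no relatives) | 0.99-1.02 | 0.99-1.02 |
| 2 | 1.02-1.03 | 0.99-1.01 |
| 3 | 1.07-1.12 | 1.03-1.08 |
| 5 | 1.10-1.17 | about 1.08 |

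The m = 1 row shows simulation noise of about 2%, so the m = 2 effect is barely detectable for the continuous outcome and not detectable for obesity.

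**3. Array or ancestry left out**

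Take a two-level factor, half the sample in each level, that shifts the GPS by dx SD and, apart from the GPS, shifts BMI by dy SD (both assumed). Slope bias = 0.25·dx·dy/(1 + 0.25·dx²), against a GPS slope of √0.09 = 0.30 SD per SD. With about 67,305/2 ≈ 33,650 per sex (equal split assumed), the slope's standard error is √(0.91/33,650) = 0.0052.

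| dx | dy | Bias | Share of slope | In standard errors |
|---|---|---|---|---|
| 0.05 | 0.05 | 0.0006 | 0.2% | 0.1 |
| 0.1 | 0.2 | 0.0050 | 1.7% | 1.0 |
| 0.2 | 0.3 | 0.0149 | 5.0% | 2.9 |
| 0.5 | 0.3 | 0.0353 | 11.8% | 6.8 |

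If either shift is zero, this bias is zero. With a sample this large, a bias that is small relative to the slope can still exceed sampling error.

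**The case against.** The strongest reply is that a protocol commonly leaves array indicators, principal components and variance estimators to the statistical analysis plan, which is not at hand and may contain them. This stands in part: the absence of genetic covariates here does not show that they will be left out. The level of clustering is different. The protocol states it outright, alongside the age terms, the sex split and the sensitivity analyses, and followed as written it leaves relatives independent.

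Three stronger readings are tempting, and the protocol supports none of them.

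- *That the models adjust for nothing but age.* Age is the only named covariate, but sex is handled by separate fits, weight is related to average height, and time enters the GEE analysis.
- *That every interval is materially too narrow.* With four relatives per family and a residual correlation of 0.3, DE = 1 + 3·0.5·0.3 = 1.45, which makes standard errors 17% too small and coverage 89.6%. But opposite-sex relatives never share a model, so this needs four genotyped same-sex relatives per family, and nothing in the protocol suggests that. It also applies a slope formula to a contrast of tenths.
- *That array or ancestry confounds the time trend.* A person's score and array are the same at every measurement, including those linked from 1963-75. The trend could be distorted only if array or ancestry also followed birth cohort or participation and was related to BMI. The protocol does not report how arrays were allocated or how ancestry varies.

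**Conclusion.** The point holds in a limited form: the model as written is incomplete, but it is not shown to be biased. With about two same-sex relatives per family and heritability of 40-60%, GPS slope standard errors should be about 4-7% larger and coverage is about 93-94%. The obesity contrast between extreme tenths is close to unaffected at that family size, and its standard error is about 8% too low with five. Family size is the deciding assumption and the protocol gives no figure for it. Resemblance through shared environment, not counted here, would raise the numbers.

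Confounding by array or ancestry is conditional. For assumed shifts up to 0.2 SD in the GPS and 0.3 SD in BMI it is at most about 5% of the slope, though this would be 2.9 standard errors. It should be addressed because the remedy is standard and cheap, not because the main conclusions are likely to reverse.

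**What to change.** In the Statistical Analysis part of Method:

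- Add genotyping array and the leading ancestry principal components as covariates in all GPS models, including the sensitivity analyses that use the GPS.
- Identify relatives from the genotype data and use robust variances clustered on family, or a family random effect; or repeat the main model in unrelated participants.
- If the statistical analysis plan already does this, refer to it from the protocol.

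The genotype data are already held, so the cost is a little analysis work and slightly wider intervals. A repeat in unrelated participants also uses fewer people. If the results barely move, the analysis will have shown that relatedness and structure do not matter here.

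### With the usual model-based standard errors, the linear mixed model for obesity gives intervals too wide where obesity is rare and too narrow where it is common; the protocol should name a robust variance

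*Protocol*

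**What the plan says.** Under Method, Statistical Analysis, the protocol analyses obesity as a dichotomous variable "using linear mixed models with observations clustered within individuals, and with a random slope for age", separately for men and women. On age it adds: "We will adjust for age using linear splines". From this model the authors will "graph the estimated prevalence of obesity for the highest compared to lowest tenth of genetic susceptibility for chosen ages at each decade".

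They recognise the nature of the model ("Using a linear model on a dichotomous outcome gives us a linear probability model") and justify it by ease of interpretation. They acknowledge one drawback: "we risk having confidence intervals including impossible values of probabilities below null".

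As the first sensitivity analysis, "we will analyze the associations between genetic risk, age and time using generalized estimation equation (GEE). This will allow us to use a logistic model", and "By use of postestimation commands (margins), we can predict the probability of obesity in the population for different groups".

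The protocol states neither the residual variance structure of the mixed model nor whether its standard errors are model-based or robust.

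**The concern.** A yes/no outcome with prevalence p has variance p(1-p). The planned figure sets side by side the cells where p differs most: the two extreme tenths, in decades before and after the obesity epidemic. A linear mixed model fitted in the ordinary way has a single residual variance, which is in effect an average over all cells. That average is too large for rare cells and too small for common ones.

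Limits below zero are the visible half of this problem. The half the protocol does not mention is intervals that are too narrow in the highest tenth in later decades. The introduction names absolute obesity risk in the top decile as a main aim, so the estimates of most interest would look more certain than they are.

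**Working it through.** **Figures in the protocol.** It gives no obesity prevalence, standard error, power or within-person correlation, so there is no stated result to reproduce. It gives 67,305 participants with genetic data (Study population) and ten equal groups (Genotyping section). That is about 6,730 per tenth, or about 3,365 per tenth and sex if the sexes are equal in number (assumption). All prevalences below are assumptions.

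**Step 1: closed form.** With one pooled variance, the ratio of reported to correct standard error in a cell is sqrt(mean[p(1-p)] / (p(1-p))), and the coverage of a nominal 95% interval is 2Φ(1.96 × ratio) - 1. Take four survey periods, with p = 1, 2, 3, 5% in the lowest tenth and 4, 8, 17, 28% in the highest.

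- The values of p(1-p) are 0.0099, 0.0196, 0.0291, 0.0475 and 0.0384, 0.0736, 0.1411, 0.2016. Their mean is 0.5608/8 = 0.0701.
- Lowest tenth, first period: sqrt(0.0701/0.0099) = 2.66.
- Highest tenth, last period: sqrt(0.0701/0.2016) = 0.59, so coverage is 2Φ(1.156) - 1 = 75%.

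Other assumed ranges give the same pattern:

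| Assumed prevalences | Ratio at the lowest p | Ratio at the highest p | Coverage at the highest p |
|---|---|---|---|
| 1-12% | 2.19 | 0.67 | 81% |
| 1-25% | 2.88 | 0.66 | 81% |
| 2-40% | 2.46 | 0.70 | 83% |

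**Step 2: simulation of the planned type of model.** The closed form ignores the random effects, so the mixed model itself was simulated: 0/1 outcome, ten tenths by four periods, linear age spline, random intercept and random age slope, one residual variance. Assumptions were 200 people per tenth, 70% of visits observed and a latent within-person correlation of 0.8. There were 250 runs for the mid scenario (the prevalences of step 1) and 120 each for low and high. Ratios are the model-based standard error over the empirical standard deviation of the estimate.

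| Quantity | Low | Mid | High |
|---|---|---|---|
| Lowest tenth, assumed p | 0.3-2% | 1-5% | 2-10% |
| Lowest tenth, ratio | 1.71-2.56 | 1.40-1.94 | 1.30-1.90 |
| Highest tenth, last period, assumed p | 16% | 28% | 42% |
| Highest tenth, last period, ratio (coverage) | 0.60 (75%) | 0.63 (79%) | 0.70 (83%) |
| Gap between tenths, first period, ratio | 0.97 | 1.13 | 1.06 |
| Gap, last period, ratio (coverage) | 0.77 (83%) | 0.80 (90%) | 0.88 (91%) |
| Change in gap, ratio (coverage) | 0.83 (89%) | 0.89 (92%) | 0.92 (95%) |

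Coverage in the lowest tenth was 98-100%. The Monte Carlo standard error of the coverages near 75-83% is about 3 to 4 percentage points; for example, sqrt(0.75 × 0.25/120) = 0.040.

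Two smaller simulations of the same kind of model agree in direction. One (40 runs, assumed p 1-30%, some convergence warnings) gave ratios down to 0.73 in the highest tenth. The other (8 runs, p = 45%, compared with the binomial standard error) gave 0.77, which implies coverage of 2Φ(1.509) - 1 = 87%.

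**Step 3: absolute size.** The correct half-width is 1.96 × sqrt(p(1-p)/3,365), treating a cell as 3,365 independent people.

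- p = 28%: 1.52 percentage points. The default interval would give 1.52 × 0.63 = 0.96.
- p = 1%: 0.34 points. The default would give about 0.65 (ratio 1.94), so the limit stays above zero.
- p = 0.3%: 0.18 points. The default would give 0.18 × 2.56, about 0.47. The lower limit becomes negative only because the standard error is wrong.

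**Step 4: robust variance on the same model.** With cluster-robust standard errors, the ratio to the empirical standard deviation was 0.94-1.06 in the mid scenario and 0.81-1.10 over all scenarios. Coverage in the last-period highest tenth rose to 93-95%. In the rarest cells (p = 0.3-1%) it was still only 64-78%, but those cells expected just 200 × 0.7 × 0.003 = 0.4 to 200 × 0.7 × 0.01 = 1.4 events. With 3,365 people all observed, the same prevalences give about 10 to 34 events.

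**The case against.** The strongest objection is that the premise is not on the page. A reader might infer that the protocol prescribes one constant residual variance and that its intervals are therefore wrong. It prescribes no such thing. Constant residual variance is the usual default for this model, and the random age slope lets total variance change with age. A robust option could also be set in an analysis plan that is not shown. This stands, and it makes the finding conditional. It does not dispose of it: the protocol fixes the model, draws the main figure from it and discusses its intervals, yet names only limits below zero. The random slope was in the simulated model and the distortion remained, because the variance also differs by tenth and period.

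A second objection is that the logistic GEE is already planned and respects the binary variance. True, but as a sensitivity analysis it does not correct the intervals on the main figure. Making it primary is a debatable trade-off, since it changes the missing-data assumptions for people with unequal numbers of measurements.

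Third, a reader might take the single-cell ratios as the error in the comparison of tenths, or expect the study's conclusions to change. Neither is supported. The gap and its change over time are distorted less, the absolute errors are modest at the available sample size, and nothing here shows a conclusion reversed.

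**Conclusion.** The concern holds in conditional form. If model-based standard errors are used, the graphed prevalences carry intervals of about 1.3 to 2.6 times the correct width in the lowest tenth; the upper end comes from an assumed prevalence of 0.3%. In the highest tenth in the last period the intervals are about 0.6 to 0.8 of the correct width. The direction was the same in every scenario for the lowest tenth and for the highest tenth in the last period. The sizes rest on assumed prevalences, and in the main simulation on an assumed within-person correlation of 0.8; the documents give neither. The ratios in the closed form do not depend on sample size, so the large cohort does not cure the problem. Severity: should be fixed, because the affected estimates are the top-decile absolute risks that the study sets out to report.

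**What to change.** Keep the linear probability model and its absolute scale. Add one sentence to Statistical Analysis stating that all confidence intervals from it use cluster-robust (sandwich) variances, clustered on the person. Show the already planned logistic GEE predictions beside the main figure for cells where obesity is very rare, because robust intervals from a linear model can still cross zero or under-cover there.

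The cost is one sentence, one software option and an added display; no new data are needed. Intervals for the highest tenth in later decades will be wider, for example about 1.52 instead of 0.96 percentage points on each side at an assumed prevalence of 28%. If robust variances are already specified elsewhere, a cross-reference and the added display are enough.

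### Early weights come only from people who later reached HUNT2 or HUNT3; the test-then-restrict safeguard against this selection is partial and should become analyses that are always reported

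*Protocol*

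**What the plan says.** The Protocol (Method, Study population) builds the cohort from "participants in the Nord-Trøndelag Health Study (HUNT, 1984-2008) linked to previous height and weight measurements for the same individuals", the earlier source being the Tuberculosis Screening Program of 1963-75. It counts "118,959 HUNT participants aged 13-80 with valid height and weight measurements of whom 67,305 had genetic data available". Under the genotyping heading it adds: "For adult participants in HUNT2 and HUNT3, genotyping was performed". A person seen only at screening and at the first HUNT survey (HUNT1, taken here as the start of the 1984-2008 window) therefore has no polygenic score.

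The introduction asks whether secular trends changed the risk of the most genetically predisposed, and whether the score is stable before and after the obesity epidemic. The Statistical Analysis section contrasts the highest and lowest genetic tenths at chosen ages in each decade.

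The safeguard is the second sensitivity analysis: "we will assess the probability of having genetic data available (i.e. participating in HUNT2 or HUNT3) based on the obesity status of participants in TBC-screening". The consequence is: "An association will indicate a possible selection bias, and will be handled by restricting the sample to younger cohorts". The Protocol gives no criterion for an association, no adjustment for age and no birth-year cut.

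**The concern.** Selection is tied to calendar time, the axis of the main comparison. A screening weight enters the score analysis only after decades of survival and continued participation. A HUNT1 weight also needs later participation. A weight measured at HUNT2 or HUNT3 needs nothing further. If heavier people were less likely to be genotyped later, obesity in the early decades would be understated, and by more percentage points in the top tenth, where it is commoner. The early gap would be too small, and the gap would seem to grow even with no true change. That is the pattern the study sets out to look for.

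The safeguard has four weak points:
- A null result leaves the analysis untouched.
- Obesity is dichotomised and no age adjustment is stated, so an association may reflect age alone.
- The only remedy discards early measurements at older ages.
- If screening data exist only for people who joined HUNT, losses between screening and 1984 cannot be seen.

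**Working it through.** The Protocol gives no figure for this selection, so none can be reproduced. Steps 2 to 4 are illustrations on stated assumptions.

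**1. Arithmetic on the Protocol's figures.** Genotyped: 67,305/118,959 = 56.6%. Not genotyped: 118,959 − 67,305 = 51,654 (43.4%). From screening to the start of HUNT: 1984 − 1975 = 9 years to 1984 − 1963 = 21 years.

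**2. What the check sees, by period of selection.** Assumptions:
- Mortality hazard 3×10⁻⁵·exp(0.095·age).
- 15 years from screening to HUNT1, then 11 years to the genotyped survey.
- Early obesity 20% in the top tenth and 5% in the bottom, so the true gap is 15.0 points.
- Obesity multiplies mortality by a hazard ratio (HR).

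Observed prevalence in a tenth with true prevalence p is p·S_o / [p·S_o + (1 − p)·S_n], where S_o and S_n are survival to genotyping in obese and non-obese people.

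Example: age 60 at screening, HR 1.6 after HUNT1 only, so that survival before HUNT1 cancels, with S_o = 0.314 and S_n = 0.485.
- Top: 0.0628/(0.0628 + 0.3880) = 13.9%.
- Bottom: 0.0157/(0.0157 + 0.4608) = 3.3%.
- Gap 10.6 points, bias −4.4.
- Check odds ratio among HUNT joiners: (0.314/0.686)/(0.485/0.515) = 0.49.

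| Selection acts | Check odds ratio, age 25 to 60 | Bias in early gap (points), age 25 / 40 / 50 / 60 |
|---|---|---|
| Before HUNT1 only, HR 1.6 | 1.00 at every age | −0.1 / −0.3 / −0.8 / −1.9 |
| After HUNT1 only, HR 1.6 | 0.62 to 0.49 | −0.2 / −0.7 / −1.8 / −4.4 |
| Both, HR 1.3 | 0.77 to 0.68 | −0.1 / −0.5 / −1.3 / −3.2 |
| Both, HR 1.6 | 0.62 to 0.49 | −0.2 / −1.0 / −2.5 / −5.8 |
| Both, HR 2.0 | 0.49 to 0.33 | −0.4 / −1.7 / −4.0 / −8.6 |

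The check is blind only when selection is confined to the years before HUNT1. Bias is small in people who were young at screening.

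**3. Age alone can produce an association.** Suppose obesity has no effect on survival but rises with age: 2.5%, 7%, 10% and 13% at screening ages 25, 40, 50 and 60, with equal numbers of HUNT joiners at each age. Under the same mortality, the probability of being genotyped is 0.974, 0.897, 0.756 and 0.485.
- Obese: (0.0244 + 0.0628 + 0.0756 + 0.0631)/0.325 = 0.695.
- Non-obese: (0.9497 + 0.8342 + 0.6804 + 0.4220)/3.675 = 0.785.
- Crude odds ratio: (0.695/0.305)/(0.785/0.215) = 0.62. Within each age it is 1.00.

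**4. Size with no remedy, and what weighting recovers.** Simulation of 4 million people: BMI = mean + 1.2·score + N(0, SD 3.6). The probability of being genotyped is logistic in BMI: 70% or 50% at mean BMI, with odds of not being genotyped 1.5 or 2.0 times higher per 5 kg/m².

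| Genotyped at mean BMI; odds | Mean BMI 25 (obesity 9.4%): true gap 18.8, observed | Check odds ratio | Mean BMI 22.5 (obesity 2.4%): true gap 6.5, observed |
|---|---|---|---|
| 70%; 1.5 | 16.4 | 0.56 | 5.2 |
| 70%; 2.0 | 14.3 | 0.37 | 4.1 |
| 50%; 1.5 | 15.1 | 0.55 | 4.7 |
| 50%; 2.0 | 12.3 | 0.36 | 3.4 |

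At mean BMI 25 the apparent loss is 18.8 − 16.4 = 2.4 to 18.8 − 12.3 = 6.5 points. The mean BMI gap falls by only 2-6%, so the obesity outcome is the vulnerable one. Weighting by the true inverse probability of being genotyped restores the gap to 18.8.

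**The case against.** The strongest reply is that the plan already targets this bias. The check models genotyping on early obesity and has ungenotyped participants to compare with. Steps 2 and 4 show that it would see most plausible selection: odds ratios of about 0.3 to 0.8 when selection acts after HUNT1, and 0.36 to 0.56 in the simulation. With an assumed 5,000 screened people, the latter correspond to z values of about 6 to 10, so the remedy would be triggered. The remedy also works in part, since bias of 3-9 points at screening age 60 is under 0.5 at age 25. All of this stands.

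Four stronger readings are therefore not supported:
- **That the check can neither see nor correct survivor selection.** It misses only selection confined to the years before HUNT entry, and the restriction reduces the bias.
- **That 2.4-6.5 points of spurious widening would remain under the plan.** That is the bias with no remedy at all.
- **That 43% is survivor loss.** The denominator covers everyone aged 13-80 in HUNT, and genotyping was for adults in HUNT2 and HUNT3. The ungenotyped may include adolescents and others with no screening measurement. The Protocol does not give the share lost among screened people.
- **That older ages vanish from the figures.** The Protocol promises only chosen ages. Restriction removes early measurements at older ages, so the secular comparison at those ages is lost.

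Two further replies carry some weight. Age adjustment, the criterion and the cohort cut may be in an analysis plan that is not shown. And the check's wording could mean everyone screened, although the Study population text describes linkage only for HUNT participants. Neither reply changes the conditional rule, which the Protocol itself fixes.

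**Conclusion.** The point holds in limited form. The documents show that early measurements in the score analysis are conditional on later survival and participation while the latest ones are not, and that the only safeguard is a conditional check on dichotomous obesity followed by discarding older cohorts. The safeguard has value but is incomplete. A null result ends the matter, an association may be age alone (crude odds ratio 0.62 with no true effect in step 3), and early measurements at older ages are lost. On the linkage as described, losses over the 9 to 21 years before 1984 are invisible; in the illustration with HR 1.6, selection confined to that period biases the early gap by 0.1 to 1.9 points.

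Size and direction cannot be taken from the Protocol. The figures assume that heavier people are less likely to be genotyped; the opposite would reverse the bias. The improvement is cheap and worth making because the assumed bias would resemble the result of interest. It does not show that the planned analysis is invalid.

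**What to change.** Replace the test-then-act rule. Always report, beside the main model:
1. The analysis restricted to birth cohorts on the younger side of a birth-year cut fixed in advance.
2. An inverse-probability-weighted version of the main model, with weights for having genetic data given age, sex, survey and continuous BMI at screening and HUNT1.

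If the check itself is kept, make it descriptive, adjust it for age and use continuous BMI.

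State whether the check covers everyone screened or only those who joined HUNT. If only joiners, say that selection before 1984 cannot be tested with these data and limit the early-decade conclusions accordingly. Do not present the 43% without genetic data as survivor loss.

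Cost: some extra analysis on data already held, and slightly wider intervals. Weighting needs a correctly specified model for genotyping and does not recover losses before 1984, so the stated limitation is still needed.
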